## Abstract

**Background:** This proposal aims to explain some of the gaps in scientific knowledge on the natural history of coronavirus disease (COVID-19), with a specific focus on immune, inflammatory, and metabolic markers, in parallel with temporal assessment of clinical and mental health in patients with COVID-19. The study will explore the temporal modulatory effects of physical activity and body composition on individual trajectories. This approach will provide a better understanding of the survival mechanisms provided by the immunomodulatory role of physical fitness. **Methods:** We will conduct a prospective observational cohort study including adult patients previously infected with the SARS-CoV-2 virus who have expressed a mild to moderate COVID-19 infection. Procedures will be conducted for all participants at baseline, six weeks after vaccination, and again at 12 months. At each visit, a venous blood sample will be collected for immune phenotypic characterization and biochemistry assays (inflammatory and metabolic parameters). Also, body composition, physical activity level, cardiovascular and pulmonary function, peripheral and respiratory muscle strength, functional exercise capacity, and mental health will be evaluated. Using the baseline information, participants will be grouped based on physical activity levels (sedentary versus active), body composition (normal weight versus overweight or obese), and SARS-CoV-2 status (positive versus negative). A sub-study will provide mechanistic evidence using an in-vitro assay based on well-trained individuals and age-matched sedentary controls who are negative for SARS-CoV-2 infection. Whole blood will be stimulated using recombinant human coronavirus to determine the cytokine profile. Peripheral blood mononuclear cells (PBMCs) from healthy well-trained participants will be collected and treated with homologous serum (from the main study; samples collected before and after the vaccine) and recombinant coronavirus (inactive virus). The metabolism of PBMCs will be analyzed using Respirometry (Seahorse). Data will be analyzed using multilevel repeated-measures ANOVA. **Conclusions:** The data generated will help us answer three main questions: (1) Does the innate immune system of physically active individuals respond better to viral infections compared with that of sedentary people? (2) which functional and metabolic mechanisms explain the differences in responses in participants with different physical fitness levels? and (3) do these mechanisms have long-term positive modulatory effects on mental and cardiovascular health? Trial registration number: Brazilian Registry of Clinical Trials: RBR-5dqvkv3. Registered on 21 September 2021.

## 1. Background

A high number of individuals who did not require hospitalization continue to present with sequelae months after contracting mild or moderate Coronavirus disease (COVID-19) [1]. The most common symptoms are fatigue, dyspnea, anosmia, ageusia, headaches, chest and muscle-skeletal pain, exercise intolerance, palpitations, memory loss, and mood changes [1,2]. Therefore, the presence of a “long-COVID” syndrome highlights the need for long-term health follow-up in a subgroup of patients with mild to moderate COVID-19 form who are often overlooked.

The etiology of COVID-19 progression involves interaction between the virus and angiotensin-converting enzyme 2 (ACE2) receptors which are present on cells in nearly every human tissue, suggesting vast consequences for general human physiological functions. Early investigations revealed that severe acute respiratory syndrome coronavirus 2 (SARS-CoV-2) primarily infected the lungs and then spread via the blood circulatory system to different organs and systems, causing dysfunction in musculoskeletal, cardiac, and nervous systems homeostasis [3]. Furthermore, prolonged systemic cytokine-induced inflammatory response and propagation can have deleterious effects downstream of the initial viral infection in the lung, possibly causing severe physiological impairments. On the other hand, physical inactivity (sedentarism) and overweight/obesity can cause greater vulnerability to the immune system and an increased probability of disease progression and subsequent adverse events after infection. However, the effects of physical activity on long-COVID are not well documented.

The benefits of physical activity are well documented and include a reduction in metabolic diseases, cardiovascular diseases, viral infections, and oncological diseases [4]. Regular physical activity is also believed to positively modulate the immune system’s ability to deal with infections. Active individuals seem to have improved immunity when it comes to the recognition and elimination of antigens, as well as the organization of the immune response to protect from or attenuate the symptoms of infection [5]. Studies have linked the positive effect of the immune system and a better pro/anti-inflammatory balance to different intensities of intermittent or regular exercise sessions in subjects who exercise and/or in lifelong athletes compared with sedentary subjects [4,5,6,7,8,9,10,11]. However, we didn’t know if it provides potential protection against SARS-CoV-2 infection and/or can benefit the recovery of people infected with the virus, alleviating the symptoms. Studies of patients with severe COVID-19 have already reported increases in inflammatory monocytes and neutrophils, and a sharp decrease in lymphocytes [12,13], and an inflammatory milieu [14]. Despite these analyses, the dynamics of the immune response during SARS-CoV-2 infection in patients with mild and moderate symptoms and its association with physical activity level and body composition remain unclear.

The level of physical activity has been associated with a positive modulation of general clinical functions, including those associated with the cardiorespiratory, musculoskeletal, and nervous systems [6,8,15,16]. Lifelong physical activity has been associated with better cardiovascular function, indicating the combined effect of a reduction in peripheral vascular resistance, which may be due to neuro-humoral and structural responses, with a reduction in sympathetic nerve activity and an increase in arterial diameter [17]. This promotes better arterial compliance, from which a better buffering of the left ventricle ejection wave, lesser reflected waves, and better heart-arterial coupling are expected [18,19]. Physical activity benefits pulmonary function, mainly due to improvement in the dynamics of the respiratory system, which is promoted by the positive change in body composition and improvement in the resistance and strength of the respiratory muscles. In addition to a more efficient cardiorespiratory system promoting a better supply of oxygen and nutrients to the muscles under constant activity, the metabolic, physical, immunological, and inflammatory changes promoted by physical exercise provide improved functional capacity and quality of life. The mental health benefits of physical activity are also well established [20]. Studies have shown that physical activity is associated with a reduced risk of mental disorders, specifically depression and anxiety [21,22]. Exercise promotes physiological and psychological effects, including increasing levels of endorphins [23], production of neurotransmitters [24], the decreasing response of the hypothalamic-pituitary adrenal axis to stress [24], and promoting positive feelings associated with well-being [25]. Furthermore, it appears that the anti-inflammatory effects of exercise contribute to better mental health outcomes in patients with inflammatory disorders [26]. These are possible mechanisms through which regular physical activity could alleviate the severity of the COVID-19 pandemic, in addition to its positive effects on several chronic diseases [27].

Considering the previous rationale and the current pandemic, it is imperative to ask: What are the long-term consequences of COVID-19 and how do physical activity, body composition, immune profiles, and inflammation contribute to different trajectories of general clinical functions throughout a lifetime and overall physiological recovery? There is no data on the prevalence, nature, and behavior of COVID-19 in physically active individuals, and little is known about the long-term health consequences of COVID-19 and its relation with SARS-CoV-2 vaccination [28].

This proposal describes methods for an observational prospective follow-up investigation of adult patients previously infected with mild to moderate COVID-19, we will conduct measures 3 times, (1) baseline, (2) six weeks after full vaccination, and (3) again at 12 months. Investigations of this magnitude in individuals who previously had mild to moderate SARS-CoV-2 infection are relevant for generating data in a population that is non-severely affected by the disease, and who may suffer from sequelae that are yet to be explored, with the intention to assist in the planning of rehabilitation programs.

As is known, age and metabolic disorders are factors related to poor prognostic of the COVID-19 disease. Our idea will be to study a sub-population that exhibits low risk of severe COVID-19 disease, and that in general will be not admitted to the hospital in intensive care. However, the consequences of infection during the long term were never studied.

Our main objective is to evaluate if physical activity levels and the number of adipose tissue depots are determinants of systemic inflammatory response and general clinical functions in adults who previously suffered from mild to moderate COVID-19, before and after specific vaccination, using a cohort prospective observational study. Additionally, we will explore modulatory effects of physical activity on immune responses to the virus, focusing on the function and metabolism of peripheral blood mononuclear cells (PBMCs) after in vitro exposure to homologous serum and/or recombinant coronavirus.

## 2. Methods

The protocol is registered with the Brazilian Registry of Clinical Trials (accessed date—21 September 2021 https://ensaiosclinicos.gov.br/). Any relevant changes will be updated on the site.

### 2.1. Study Design and Setting

A study design summary displaying the steps and evaluations of potential participants over approximately 18 months of follow-up is provided in Figure 1.

A follow-up period of approximately 18 months will be implemented. The procedures will be conducted for all participants at baseline, 6 weeks after vaccination, and 12 months after vaccination. After approval by the local Research Ethics Committee, patients previously infected with COVID-19 will be contacted to participate in the study through the local media and via electronic access to the participants’ database of Municipal Health Secretariat (MHS) of Presidente Prudente—São Paulo. Male and female patients aged 20–40 years with mild or moderate clinical COVID-19 infection will be recruited (intensive care cases will be excluded). An age-matched healthy control group that is negative for SARS-CoV-2 will also be enrolled. To detect previous SARS-CoV-2 infection, a lateral flow test for IgM and IgG antibodies will be conducted using internal anti-SARS-CoV-2 IgG and IgM ELISA kits. Participant exclusion criteria will include (1) presence of chronic non-communicable diseases, (2) smokers, (3) history of drug use, (4) medications such as anti-inflammatory drugs or antibiotics, (5) and frequent alcohol consumption (more than three times a week.

At each visit, body composition will be assessed using Dual X-ray Absorptiometry (DXA), bioimpedance, and ultrasonography. Accelerometers will be used to assess habitual physical activity. The cardiovascular function will be evaluated using an electrocardiogram, Doppler echocardiogram, and heart rate variability. The pulmonary function will be evaluated by spirometry. Peripheral and respiratory muscle strength will be measured using an electronic dynamometer and manovacuometer. Functional exercise capacity will be assessed using the 6-min walk test (6MWT). Mental health will be evaluated using questionnaires. Venous blood samples will be collected for immune phenotypic characterization and biochemistry assays (inflammatory and metabolic parameters). A protocol for ex vivo stimulation of whole blood with LPS will be used to imitate an inflammatory environment for determining the level of cytokines. Serum markers and markers of early cardiovascular function will be correlated with body fat and physical activity levels. Flow cytometry will be conducted and monocytes, T cells, and Natural Killer cell subsets in whole blood will be quantified and characterized. Additionally, after characterization and correlation of the determinants of SARS-CoV-2 severity with the amount of body fat and physical activity level and based on the hypothesis that individuals with low body fat and high physical activity levels have a better clinical outcome, we will examine immune cells from well-trained subjects (higher physical activity level and low-fat body) using an in vitro experimental model and compare them with age-matched non-trained subjects (control model).

Considering the effects of intermittent and regular physical activity on the immune system that can potentially mitigate viral infections, the molecular and biochemical mechanisms of action of immune cells in response to coronavirus will be detailed. Peripheral blood mononuclear cells (PBMCs) from well-trained participants will be collected and treated with homologous serum (collected from patients before and after vaccination) and recombinant coronavirus (inactive virus). After culturing, cytokine production will be determined by Luminex. PBMCs will be cultured for 24 h and then examined for phagocytosis, and cytokine and H_2_O_2_ production. Expression of *ACE-2*, *AT1R*, *AT2R*, *MASR*, *TLR-3*, *TLR-4*, *NOS*, *CETP*, *L-CAT*, and *ABCA1* genes will be analyzed using qRT-PCR. Energy metabolism will be characterized in terms of mitochondrial oxygen consumption rates (basal respiration, ATP production-linked respiration, maximal respiration, space respiratory capacity, proton leak-related respiration, non-mitochondrial respiration, bioenergetic health index, and coupling indexes) using the Seahorse XFe96 Extracellular Flux Analyzer (Agilent, Santa Clara, CA, USA). Mitochondrial DNA and transcripts of relevant oxidative phosphorylation (nuclear and mitochondria-encoded subunits of the ATP synthase and the mitochondrial respiratory chain, adenine nucleotide translocator, and voltage-dependent anion channel) will be obtained using qRT-PCR; antioxidant enzyme (superoxide dismutase I and II, glutathione peroxidase, glutathione reductase by colorimetric methods) activity and reduced and oxidized glutathione (GASH/GSSG) will be analyzed using high-performance liquid chromatography.

All reports generated from this study will follow the Strengthening the Reporting of Observational Studies in Epidemiology principles [29].

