### 2.10. Sample Size Estimation and Planning for Data Analysis

A Cohort of participants previously infected with SARS-CoV-2 and age-matched healthy participants will be randomly selected from the target population. Sample size calculation (G*Power, version 3.0; power = 0.80; α level = 0.05; medium-size effect) provided an estimated 75 participants. Therefore, 100 male and female participants aged 20–40 years will be recruited (over-recruitment compensates for dropouts during follow-up).

Participants will be stratified based on habitual physical activity levels (assessed by accelerometry-low versus normal physical activity levels), body composition (normal weight versus overweight or obese), and SARS-CoV-2 status (positive versus negative). In addition, a sub-analysis will be stratified based on sex (men vs. women).

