## 3. Discussion

This protocol describes an ambitious follow-up study that will be conducted in adults previously infected with COVID-19 (before and after vaccination program), highlighting long-term consequences of COVID-19 and its correlation with physical activity, body composition, and cross-linked with vaccination in the Brazilian population. Our hypothesis links reduced visceral adipose tissue deposits (which exhibit an anti-inflammatory profile, as hypoleptinemia and hyperadiponectinemia) with higher physical activity levels as central factors in reducing the severity of SARS-CoV-2 aggression, promoting metabolic programming of immune cells (favoring anti-inflammatory response), protecting the cardiovascular system, and general clinical profile.

Patients with COVID-19 who were consistently inactive and malnutrition had a greater risk of hospitalization, admission to the ICU, and death due to COVID-19 compared with patients who were consistently meeting the minimum physical activity guidelines (150 min/week) [27,47,48]. Longitudinal cohort studies of individuals who developed severe COVID-19 are being conducted to investigate possible symptoms and long-term clinical and functional alterations [49,50]. Longitudinal follow-up studies reporting persistent symptoms and sequelae of COVID-19 in mild and moderate patients are also needed in order to understand the intrinsic physiological mechanisms involved in these processes, their potential protective factors, and public health policies needed for treatment in the post-pandemic period in order to substantially minimize long-term chronic sequelae.

In addition to investigating an overlooked population, one advantage of the study proposed here is that we will conduct comprehensive symptom and clinical assessments of long-COVID manifestations pre- and post-vaccination. Potential limitations include the fact that we will rule out the presence of current re-infection based only on the absence of clinical signs and symptoms, rather than on the basis of a negative RT-PCR test. We will also only assess a specific, young population.

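### Markers are to be correlated with body fat and with physical activity, two linked exposures, and no mutual adjustment is stated, so simple correlations cannot show whether each is a determinant in its own right

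*Protocol article*

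**What the plan says.** The main objective (protocol article, section 1, Background) is to find out whether "physical activity levels and the number of adipose tissue depots are determinants of systemic inflammatory response" and of general clinical function. Two exposures are thus to be judged as determinants.

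Section 2.1 names the analysis for blood and early cardiac markers: "Serum markers and markers of early cardiovascular function will be correlated with body fat and physical activity levels". Later in the same section the determinants of disease severity are also to be correlated with the amount of body fat and the activity level. No coefficient is named, and the text does not say whether the correlations are simple, partial or joint.

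The article pairs the two exposures in several places. Section 2.1 rests the sub-study on the hypothesis that "individuals with low body fat and high physical activity levels have a better clinical outcome", and defines its well-trained group by both traits at once. Section 3 (Discussion) opens its hypothesis with "Our hypothesis links reduced visceral adipose tissue deposits" and couples these with higher activity.

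The only model named is in the Abstract: "Data will be analyzed using multilevel repeated-measures ANOVA". The Abstract and section 2.10 list the grouping factors together: activity level, "body composition (normal weight versus overweight or obese), and SARS-CoV-2 status (positive versus negative"). Neither place says that the factors will enter the same model.

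**The concern.** When two exposures are correlated, the simple correlation of a marker with one of them also carries whatever the other contributes. If inactive participants tend to be fatter and a marker responds to fat alone, the marker will still correlate with activity. The same holds with the roles reversed.

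The objective asks about two determinants, and simple correlations do not separate them. The study could credit activity with an effect of its own on an inflammatory marker that follows body fat only, or credit fat with an effect that belongs to activity. The issue is how the two study exposures relate to each other in an analysis that the article names. It is not a complaint about unlisted background covariates.

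**Working it through.** **Inputs from the article.** Section 2.10 gives a target of 75 participants, 100 recruited to allow for dropout, and alpha 0.05. The article gives no figure for the correlation analysis, so there is no planned number to reproduce. The 75 and 100 serve here only as sample sizes.

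**Inputs assumed.** The article gives neither the fat-activity correlation nor the fat-marker correlation. I take -0.3 to -0.5 for the first and 0.3 to 0.5 for the second, and -0.1 as a weak-link case for the first. The marker is assumed to depend on fat only, so activity has no direct effect.

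**Step 1: induced correlation.** With no direct effect of activity, r(activity, marker) = r(fat, activity) × r(fat, marker). In absolute size this is 0.3 × 0.3 = 0.09 at the low end and 0.5 × 0.5 = 0.25 at the high end. The middle case is 0.4 × 0.4 = 0.16.

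**Step 2: how often the simple correlation is significant.** By Fisher z, the shift is d = atanh(r) × √(N − 3), and the two-sided rejection rate is Φ(d − 1.96) + Φ(−d − 1.96).

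| fat-activity r | fat-marker r | induced r (absolute) | d, N = 75 | rate, N = 75 | rate, N = 100 |
|---|---|---|---|---|---|
| -0.1 | 0.3 | 0.03 | 0.25 | 6% | 6% |
| -0.1 | 0.5 | 0.05 | 0.42 | 7% | 8% |
| -0.3 | 0.3 | 0.09 | 0.77 | 12% | 14% |
| -0.4 | 0.4 | 0.16 | 1.37 | 28% | 36% |
| -0.5 | 0.5 | 0.25 | 2.17 | 58% | 71% |

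Simulation with 20,000 data sets per setting agrees. At N = 75 it gives 11.9% for -0.3/0.3, 58.7% for -0.5/0.5, and 5.9% and 6.7% for the two weak-link rows.

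**Step 3: with both exposures in one analysis.** In the same simulations, the test of activity adjusted for continuous body fat rejects in 4.4% to 5.2% of data sets, which is the nominal level.

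**Step 4: what the ANOVA would do.** Suppose both exposures are split at the median and enter together as main effects, at one visit. Under the -0.3 to -0.5 and 0.3 to 0.5 assumptions, the false-positive rate for activity is about 6% to 10% at N = 75 and 6% to 12% at N = 100. In the 0.4/0.4 case it is about 7% and 8%, against 28% and 36% for the simple correlation. What remains arises because fat still varies with activity inside each two-level group.

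**Step 5: price of joint adjustment.** The standard error of each coefficient grows by 1/√(1 − r²), where r is the fat-activity correlation. That is 1/√0.91 = 1.05 at 0.3 and 1/√0.75 = 1.15 at 0.5.

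**The case against.** **The correlations are not said to be separate.** This is true. A reader might infer that the article commits to one exposure at a time, but it does not say so, and a condensed article may leave the adjustment set to the full plan. What survives is that an unqualified statement that markers will be correlated with two things ordinarily means simple correlations, and that no adjusted analysis appears anywhere.

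**The ANOVA already covers these markers.** The Abstract's sentence excludes no outcome and follows a list of all three grouping factors, so it would be wrong to say that the ANOVA is irrelevant or does nothing. If both factors enter together, most of the problem goes. But the article does not say that they do, and the correlations in section 2.1 would still stand beside it unadjusted.

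**Body fat may lie on the pathway from activity.** Section 1 says that the benefit of activity to lung function is in part "promoted by the positive change in body composition". If the same holds for these markers, a simple activity-marker correlation contains a real indirect effect and is not false. Adjusting for fat then removes part of what activity does. This stands, and it changes the remedy: unadjusted activity estimates should be kept as total effects, not demoted to mere description. It does not rescue simple correlations as evidence of separate contributions.

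**Joint adjustment is not perfect.** If the exposure that truly matters is measured with error, some misattribution stays. With an assumed reliability of 0.7, the joint model's false-positive rate for the other exposure is about 6% to 12% at N = 75. The nominal rate in Step 3 assumes error-free exposures and a single visit.

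**Conclusion.** The concern holds in a limited form. The article plans to correlate markers with two exposures that it expects to be linked, states no mutual adjustment, and wants to know whether both are determinants. Simple correlations cannot answer that.

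The size is conditional. The 12% to 58% range at N = 75 (14% to 71% at N = 100) requires a marker driven by fat only, the assumed correlations, and separate correlations used as the evidence. With a fat-activity correlation of -0.1 the rate is close to nominal. A reader might infer that misattribution will happen often. The documents do not support this, because they give neither correlation and because a joint ANOVA, if that is what is meant, would bring the rate down to about 6% to 12%. Nor do they support calling every unadjusted activity association spurious, since part of it may be a real effect through body fat.

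The change is worth making: it is cheap, and it alters what the study can conclude about each exposure.

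**What to change.** In section 2.1, replace the correlation sentence with a stated model. Analyse each marker in one multilevel model with DXA body fat and accelerometer activity entered together as continuous terms and a participant random intercept over the three visits. Report both partial coefficients with 95% confidence intervals.

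Report the unadjusted associations alongside. State that, for activity, the unadjusted estimate addresses the total effect, which may run through body fat, and the adjusted estimate the direct effect. Base any claim that the two exposures contribute separately on the joint model only. If the ANOVA is kept, say whether the activity and body-composition factors enter the same model.

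No new measurements are needed, because body composition and accelerometry are already planned at each visit. The costs are standard errors about 5% to 15% larger for each exposure (fat-activity correlation 0.3 to 0.5 in absolute size) and an adjusted activity coefficient that leaves out any effect acting through body fat.
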